### Data collection and management

Study data will be collected and managed using REDCap (Research Electronic Data Capture) hosted at the Public Health Foundation of India [109, 110]. REDCap is a secure, web-based software platform designed to support data capture for research studies. Data will be collected using an offline mobile app on a password-protected tablet and then synced with REDCap’s secure, web-based software platform. A de-identified dataset that does not contain any information that could lead to participant identification will be made publicly available on the Central Research Data Repository of the Public Health Foundation of India and Edinburgh DataShare upon publication of the primary outcomes.

### Data quality control

Data collectors will complete a 5-day training and must pass an examination before being certified for field work. Throughout the data collection period, field supervisors will directly observe data collectors on a regular basis. The study will employ the use of Standard Operating Procedures (SOPs), which will document, in detail, all methods used to generate the data. With written consent, audio-video recordings and photographs will be taken during the study visits for the purpose of improving the quality of data collected by the study team. All Case Report Forms (CRFs) will include an entry for the person who collected the data to provide their initials.

Regular Quality Control (QC) reports will be run by the data manager to identify entry errors and missing data. To help ensure data completeness, data collectors will be prompted to go back and complete any missing values when they attempt to submit an incomplete CRF. Skip patterns will be automatically implemented in REDCap CRFs. Wherever possible, maximum and minimum limits will be implemented in REDCap CRFs (e.g., if asked to report number of days in the past week, values >7 will not be permitted).

### Statistical analysis plan

The main analyses will be intent-to-treat, i.e., participants will be analysed as assigned, regardless of their fidelity to APCNF practices. Herein the analyses for primary outcomes are described. Analyses for secondary outcomes will be analogous. Separate models will be run for each of the primary outcomes. All primary outcomes are continuous. General estimating equation (GEE) models with robust standard errors will be used to account for within-participant correlations [111]. Models will account for clustering within villages. The models will take the form of:

$$Y_{i,t}=\beta_{0}+\beta_{1}Group+\beta_{2}Time+\beta_{3}Group*Time+\beta_{4}District+\varepsilon_{i,t}$$
(1)

where group is APCNF or control, time is baseline or 12 months, and district is Kurnool or Visakhapatnam (to account for randomisation stratification). β_3_ represents the difference in the change from baseline to 12 months in the APCNF group and the change from baseline to 12 months in the control group (e.g., difference in difference).

We will evaluate whether missing data are differential between groups using t-tests. We will assume missing data to be missing at random and conduct a complete-case analysis. Inverse probability weighting will be used to account for loss to follow-up. We will run adjusted models to address potential baseline imbalance across clusters and improve precision. Covariates will be selected based on p-values for differences across groups.

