### Setting

The study will be located in four (Anakapalli, Kurnool, Nandyal, and Visakhapatnam) of Andhra Pradesh’s 26 districts selected by the research team to capture different agro-climatic zones. When the study was initiated, these geographical areas represented two districts, Visakhapatnam and Kurnool, but following district bifurcation in April 2022, these areas now represent four districts. Given how recent district bifurcation was in the state, statistics are not available for the four new districts and so hereafter, the two original districts are described. The population of Kurnool is 4.05 million (72% rural) and Visakhapatnam is 2.29 million (53% rural) [76]. The female literacy rate is 57% in Kurnool and 70% in Visakhapatnam [77]. About half of the total geographical area of Kurnool is cultivated (937,278 out of 1,765,800 hectares) and 28% of cultivated land is irrigated (263,000 hectares) [78]. In Visakhapatnam, 30% is cultivated (339,759 out of 1,116,100 hectares) and 27% of cultivated land is irrigated (90,193 hectares) [79]. The top five crops in terms of production in Kurnool are rice, jowar (sorghum), maize, red gram, and green gram [78], and in Visakhapatnam, rice, sugarcane, palm oil, betel leaves, and maize [79]. With regards to nutritional and health outcomes, the prevalence of stunting in children under 5 years of age is 51% and 31% in Kurnool and Visakhapatnam, respectively, and the prevalence of anaemia in women is 59% and 58%, respectively [77]. The prevalence of obesity including overweight (body mass index [BMI] ≥25 kg/m^2^) in women is 29% and 24% in Kurnool and Visakhapatnam, respectively, and the prevalence of diabetes is 15% and 17%, respectively [77]. These values are generally comparable to values at the state and national level (Table 2).

**Table 2 pone.0281677.t002:** Comparison of two original districts in BLOOM (co-Benefits of Largescale Organic farming On huMan health) study to state- and national-level data in India.

	Kurnool (district)	Vishakhapatnam (district)	Andhra Pradesh (state)	India (national)
Total population*	4.05 million	2.29 million	49 million	1,210.2 million
Rural population (% total)*	72%	53%	70%	65%
Female literacy rate^†^	57%	70%	67%	72%
Total land area (hectares)^‡^	1,765,800	1,116,100	16,297,000	297,319,000*
Cultivated land (% total)^‡^	53%	30%	45%	60%*
Irrigated land (% cultivated land)^‡^	28%	27%	52%	38%*

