### Selection of clusters and random allocation procedures

A list of clusters in which APCNF has not yet been implemented will be provided by RySS and the evaluation team will randomly select clusters for inclusion in the BLOOM study from this list using simple random sampling. By purposefully enrolling clusters where RySS has never before worked, we will minimise what has been described elsewhere as the ‘[NGO] reputation effect’ [83]. In a previous randomised controlled trial in India, this reputation effect–meaning prior engagement with target communities–was shown to bias intervention effectiveness by at least 30% [83].

The study will be explained to elected representatives in the village as well as other stakeholders (e.g., community health workers and Anganwadi [government childcare centre] workers) and their permission sought. Given the narrow agricultural season window, clusters will be randomised to intervention or control after recruitment and enrolment, and the list shared in confidence with RySS so that they can begin planning implementation activities for intervention clusters. No implementation activities will begin, and data collectors and participants will not be informed of the randomisation status, until the baseline assessment is complete. Randomisation will be stratified by original district (Kurnool and Vishakhapatnam).

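### Equation (1) carries the stratification factor District only as a time-constant main effect, so on complete pairs it cancels from β3 and its standard error and does not account for the stratified randomisation

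*Protocol article*

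**What the plan says.** All references are to the Protocol article.

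- **Allocation** (Selection of clusters and random allocation procedures): "Randomisation will be stratified by original district (Kurnool and Vishakhapatnam").
- **Model** (Statistical analysis plan, equation (1)): the terms are Group, Time, Group×Time and District. District appears once, with coefficient β4 and no interaction with Time. The reason given is that "district is Kurnool or Visakhapatnam (to account for randomisation stratification").
- **Effect of interest** (same section): β3 "represents the difference in the change from baseline to 12 months in the APCNF group" set against the same change in controls.
- **Estimation** (same section): "General estimating equation (GEE) models with robust standard errors will be used to account for within-participant correlations". On villages: "Models will account for clustering within villages". The analysis is complete-case, with inverse probability weights for loss to follow-up. Secondary outcomes are to be analysed in the same way.
- **Adjusted models** (same section): "We will run adjusted models to address potential baseline imbalance across clusters and improve precision".
- **Districts** (Setting): the areas were "selected by the research team to capture different agro-climatic zones".

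**The concern.** A term that does not vary over time can explain differences in level between districts. It cannot explain differences in change. Because β3 is a contrast of changes, a District main effect has nothing to act on, and equation (1) makes both districts share one time trend.

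Two stated aims are affected: accounting for the stratification, and gaining precision from adjusted models if covariates enter as main effects only. Stratified 1:1 allocation removes a district difference in change from the true sampling variance of β3. The model leaves that difference in the estimated variance. What is at stake is precision and power. An adjusted β3 that matches the unadjusted one by construction could also be mistaken for a sign of robustness.

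**Working it through.** **Inputs.** From Study design and Power calculations (with Table 5): 80 clusters, 1:1, so 40 per arm; two-sided alpha 0.025; power 80%; ICC 0.02; 20% loss. Women's dietary diversity: SD of change 1.57, 1,000 per group, detectable difference 0.29. ∑DAPs: 150 per group. Assumed, because the documents do not say: 40 clusters per district, equal cluster sizes, and a range for δ, the difference between districts in mean 12-month change.

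**1. The plan's own figure.** Analysed per arm: 1,000 × 0.80 = 800, or 20 per cluster. In SD² units, the variance of a cluster-mean change is (1 + 19 × 0.02)/20 = 0.069. The SE of the effect is 1.57 × √(2 × 0.069/40) = 0.0922. With t quantiles on 78 df (2.285 and 0.846), the detectable difference is 3.132 × 0.0922 = 0.289. Table 5 gives 0.29, so the set-up matches the plan.

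**2. Does District reach β3?** For one participant, the 12-month value minus the baseline value under equation (1) is β2 + β3·Group + error. β4·District has subtracted out. GEE fits to simulated complete pairs (80 villages of unequal size, robust SE by village) confirm this, with the same results under independence and exchangeable working correlation:

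| Data set | Terms besides Group, Time, Group×Time | β3 | SE |
|---|---|---|---|
| A | none | 0.043483 | 0.097680 |
| A | District | 0.043483 | 0.097680 |
| A | District, District×Time | 0.028993 | 0.081951 |
| B | none | 0.443348 | 0.105134 |
| B | District | 0.443348 | 0.105134 |
| B | District, covariate main effect | 0.443348 | 0.105134 |
| B | District, District×Time | 0.452365 | 0.082997 |

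The districts were simulated to change by different amounts in both sets. In a further set with one weight per participant, the SE was 0.108941 with no District, with District, and with District plus a covariate.

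**3. Size of the excess.** With districts evenly split within each arm, a difference of δ adds δ²/4 to the apparent between-village variance but nothing to the true variance of β3. Hence:

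SE ratio = √(1 + (δ²/4)/V), where V is the variance of a cluster-mean change.

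Power as written ≈ Φ(0.29/0.0922 − 2.285 × ratio), with 0.29/0.0922 = 3.145.

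Women's dietary diversity, V = 0.069:

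| δ in SD (food groups) | SE ratio | Power as written |
|---|---|---|
| 0 | 1.000 | 80% |
| 0.1 (0.16) | √(1 + 0.0025/0.069) = 1.018 | 79% |
| 0.2 (0.31) | √(1 + 0.0100/0.069) = 1.070 | 76% |
| 0.3 (0.47) | √(1 + 0.0225/0.069) = 1.152 | 70% |

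With District×Time, power stays at about 80% in every row. Because the ratio depends only on V, children's dietary diversity has the same SE ratios.

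∑DAPs: 150 × 0.80/40 = 3 per cluster, so V = (1 + 2 × 0.02)/3 = 0.347. The ratio is 1.014 at 0.2 SD and 1.032 at 0.3 SD.

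**4. Re-randomisation check, women's dietary diversity** (4,000 stratified allocations). At δ = 0 the mean SE from equation (1) was 0.0908 and the actual SD of the estimate was 0.0915. At δ = 0.47 they were 0.1050 and 0.0915, and the nominal 97.5% interval covered 98.7%.

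**5. Total ICC held at 0.02.** In step 3 the district difference comes on top of an ICC of 0.02. If it is instead half of that ICC (δ²/4 = 0.01, δ = 0.2 SD), the true V is 0.069 − 0.010 = 0.059 and the true SE is 1.57 × √(2 × 0.059/40) = 0.0853. Power as written is Φ((0.29 − 2.285 × 0.0922)/0.0853) = 82%. With District×Time it is Φ(0.29/0.0853 − 2.285) = 87%.

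**The case against.** Four points count against a stronger reading.

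- **A reader might infer that the intervals for β3 are too wide as such.** They are not. With equal change in both districts the SE is right (step 4). The documents give no district-specific change and no split of clusters between districts. This stands in full.
- **A reader might infer that the trial falls short of the power in Table 5.** The 76% and 70% figures add the district difference to an ICC of 0.02. That makes the total roughly 0.02 + 0.01 = 0.03 and 0.02 + 0.0225 = 0.042. With total ICC at the planned 0.02, power as written remains above 80% (step 5), and District×Time is a gain on top. This also stands. In addition, a difference of 0.31 food groups would already exceed the 0.29 effect being sought.
- **A reader might argue from season and climate that a difference is likely.** The main assessments are all in monsoon cultivation (Study design), so a stable seasonal pattern cancels from the change. Different agro-climatic zones imply different levels, but not by themselves different year-to-year trends. A difference is possible, but its size is unknown.
- **The exact cancellation depends on implementation.** The article does not say how the weights or covariates enter, or that complete-case means both visits observed. With baseline rows of lost participants kept, District did move the SE slightly in simulation (0.0983 to 0.0972), against 0.0874 with District×Time. Weighting only the 12-month rows let a covariate main effect change β3 (−0.134 to −0.070 in one simulated set). So it cannot be said that adjusted models would never move β3.

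The objection does not rescue the printed rationale. Equation (1) is written out in full, District is a main effect in it, and on complete pairs that term does nothing for β3.

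**Conclusion.** The point holds as a mismatch between the model and its stated purpose. On complete pairs with participant-constant weights, District as entered has no effect on β3 or its robust SE, so equation (1) does not account for the stratification in the primary effect. Under the same conditions, covariates entered only as main effects give no gain in precision.

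The consequence is conditional and conservative: no bias in β3 and no inflation of type I error from this source. Given 40 clusters per district and a within-district ICC of 0.02, the SE for dietary diversity is too large by 0% to about 15% over district differences of 0 to 0.3 SD. For ∑DAPs the excess is about 1–3% at 0.2–0.3 SD. Where in that range the trial lies cannot be found from the documents.

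**What to change.** Add District×Time to equation (1) for the six primary outcomes and the analogous secondary models:

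Y = β0 + β1 Group + β2 Time + β3 Group×Time + β4 District + β5 District×Time + ε

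In the adjusted models, enter each covariate together with its Time interaction. Alternatively, model the 12-month value, where District and the covariates do their work as main effects.

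The cost is one degree of freedom out of 80 clusters for District×Time, one more per covariate interaction, and a sentence of text. No new data are needed. If the districts change equally, simulated power for women's dietary diversity is practically the same with the term as without it (80.2% against 80.3%).

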### Study design

This study is a community-based, cluster-randomised controlled evaluation with two parallel groups: APCNF (‘intervention’) versus conventional practices (‘control’). A total of 80 clusters will be randomly allocated 1:1 to intervention or control. The study will run for 48 months, including evaluation development and setup; baseline, midline, and endline assessments; intervention implementation (24 months); laboratory measurements of biomarkers; and statistical analysis. The main study assessments will be conducted during monsoon cultivation (July-December) with a brief survey also conducted after the monsoon harvest (January-February). The same random subset of households enroled at baseline from each cluster will be followed at 12 and 24 months post-baseline assessment.

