### Selection of evaluation participants

The sample will be selected via random selection of 34 households per cluster from a roster of households in each cluster with a child <3 years of age. Rosters will be obtained by conducting a comprehensive household listing in each cluster based on lists provided by Anganwadi workers. In the event that a cluster has fewer than 34 eligible households, all eligible households will be enroled.

Three participants will be enroled from each household: an adult male, adult female, and child. The parents of the child, if eligible, will be enroled. Eligibility criteria are summarised in Table 3. If one or both parents of the child are not available or not eligible, we will enrol the oldest eligible male or female in the household. If more than one child is eligible in a given household, we will enrol the oldest eligible child.

**Table 3 pone.0281677.t003:** Participant eligibility criteria for the BLOOM (co-Benefits of Largescale Organic farming On huMan health) study, a cluster-randomised controlled evaluation of Andhra Pradesh Community-managed Natural Farming in India.

	Adults	Children
**Inclusion criteria**	1. Household engaged in agriculture work defined as any one or more of the following: owning land, harvesting a crop in the past month regardless of land ownership, or earning a daily wage or contract-based wage for agricultural activities. This includes farmers, farm owners, farm workers, field workers, growers, harvesters, packers, graders and sorters, as well as agricultural pesticide handlers (mixers, loaders, cleaners and sprayers). 2. Aged ≥18 years. Age will be confirmed by directly viewing a government-issued document with the individual’s date of birth. 3. Permanently reside in the selected household. ‘Residence’ will be defined as a group of people who eat from the same kitchen. 4. Have a child aged <38 months old who also resides in the household. 5. Willing to provide informed consent.	1. Aged <38 months. Age will be confirmed by directly viewing a government-issued document with the child’s date of birth. 2. Permanently reside in the selected household. ‘Residence’ will be defined as a group of people who eat from the same kitchen. 3. Parent or legal guardian willing to provide informed consent.

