### Primary outcomes

Urinary pesticide metabolites at 12 months in a 15% random subsample of adult men enroled in the study. Six common dialkylphosphate (DAP) metabolites of organophosphorus insecticides will be measured in an equal-volume composite urine sample consisting of two spot urine samples collected within a one-week period. Compositing samples reduces intra-person variability. The six DAPs will include: dimethylphosphate (DMP), dimethylthiophosphate (DMTP), dimethyldithiophosphate (DMDTP), diethylphosphate (DEP), diethylthiophosphate (DETP), and diethyldithiophosphate (DEDTP). Together, these six DAPs cover approximately 77% of organophosphorus insecticides produced in India (Table 4) [11]. Total DAP molar weight (∑DAPs) will be calculated by multiplying the concentration of each of the six DAPs by the molar weights of the respective DAP and summing them. Specific gravity-adjusted ∑DAPs will be analysed as the primary outcome. Specific gravity will be measured in the composite urine sample using a handheld refractometer (Atago PAL-10S). Urine aliquots will be shipped on dry ice to the laboratory for analysis in random sequence using gas chromatography-mass spectrometry (GC-MS) [84]. Laboratory technicians will be blinded to the randomisation status of samples.Urinary pesticide metabolites at 12 months in a 15% random subsample of adult women enroled in the study. The same method, as described above for adult men, will be used to assess specific gravity-adjusted ∑DAPs in adult women.Urinary pesticide metabolites at 12 months in a 15% random subsample of children enroled in the study. The same method, as described above for adult men, will be used to assess specific gravity-adjusted ∑DAPs in children.Dietary diversity score at 12 months in all adult men enroled in the study. Dietary intake of adults will be assessed using a single 24-hour dietary recall. Participants will be taken through the previous day from morning to evening and asked to recall all foods and beverages consumed and the portion size. A standard set of locally appropriate plates, bowls, and cups and show cards will be used to aid portion size estimation. Dietary diversity will be calculated using the FAO’s Minimum Dietary Diversity for Women (MDD-W) [85]. Ten food groups are included: (1) starchy staples (rice, wheat, and potatoes), (2) legumes and pulses, (3) nuts and seeds, (4) dark green leafy vegetables, (5) vitamin-A rich fruits and vegetables, (6) other vegetables, (7) other fruits, (8) dairy products, (9) eggs, and (10) flesh foods (meat, poultry, and fish). For analysis, men who consume a food group on the previous day will be assigned a value of 1 and those who do not will be assigned a value of 0 and the values across these ten food groups will be summed in a dietary diversity score. Thus, the dietary diversity score can range from 0 to 10 with 10 representing maximum dietary diversity.Dietary diversity score at 12 months in all adult women enroled in the study. The same method, as described above for adult men, will be used to assess dietary diversity in adult women.Dietary diversity score at 12 months in all children enrolled in the study. Dietary intake of children will be assessed using the standard WHO Infant and Young Child Feeding practices survey [86], adapted to the local context and administered to the primary caregiver of the child. Dietary diversity will be calculated using the WHO’s dietary diversity score (DDS). Whilst this was originally developed for children 6–23 months old, DDS can serve as an adequate proxy for micronutrient intake in children 24–59 months as well [87]. Eight food groups are included: (1) breast milk, (2) grains, roots, tubers, and plantains, (3) pulses, nuts, and seeds, (4) vitamin-A rich fruits and vegetables, (5) other fruits and vegetables, (6) dairy products, (7) eggs, and (8) flesh foods (meat, poultry, and fish). For analysis, children who consume a food group on the previous day will be assigned a value of 1 and those who do not will be assigned a value of 0 and the values across these eight food groups will be summed. Thus, DDS can range from 0 to 8 with 8 representing maximum dietary diversity.

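### The primary model estimates a baseline group difference that randomisation sets to zero in expectation; adjusting for the baseline outcome targets the same effect more precisely

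*Protocol article*

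**What the plan says.** The Statistical analysis plan section prints the model for the primary outcomes as equation (1): intercept, Group, Time, Group×Time and District. Its terms are defined as "where group is APCNF or control, time is baseline or 12 months, and district is Kurnool or Visakhapatnam (to account for randomisation stratification". The treatment effect is β3, "the difference in the change from baseline to 12 months in the APCNF group and the change from baseline to 12 months" among controls, which the text itself calls a difference in difference. Estimation is stated as "General estimating equation (GEE) models with robust standard errors will be used to account for within-participant correlations", with clustering by village also accounted for. Secondary outcomes are to be analysed analogously.

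The same section adds: "We will run adjusted models to address potential baseline imbalance across clusters and improve precision". It then says: "Covariates will be selected based on p-values for differences across groups". The baseline outcome is not named as a covariate, and these models are not said to be primary.

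On design, the Study design section states "A total of 80 clusters will be randomly allocated 1:1 to intervention or control" and follows the same households throughout. The section on selection of clusters says that implementation starts, and collectors and participants learn the allocation, only after baseline is complete.

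On measurement, the Primary outcomes section says "Dietary intake of adults will be assessed using a single 24-hour dietary recall". ∑DAPs come from a composite of two spot urines taken within a week. The child inclusion criterion in Table 3 is "1. Aged <38 months".

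**The concern.** With random allocation and a masked, pre-implementation baseline, any baseline difference between arms is chance. Equation (1) nevertheless estimates that difference (β1) and removes all of it from the 12-month difference. A baseline-adjusted analysis removes only the part that baseline predicts. When baseline predicts the 12-month value poorly, full subtraction adds noise. If r is below 0.5, it is less precise than ignoring baseline altogether.

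One recall, or one week's urine, repeated a year later makes a low-to-moderate correlation plausible. At stake is precision in all six primary comparisons, using data the trial collects anyway. ∑DAPs, with 150 per arm, has least to spare.

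**Working it through.** **1. Reproduce Table 5.** Inputs from the Power calculations section: SD of change 1.57 (women's dietary diversity) and 111 (adult ∑DAPs); 1000 and 150 per arm; ICC 0.02; two-sided alpha 0.025; 80% power; 20% loss. With 40 clusters per arm and m people per cluster,

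MDD = SD × sqrt(2[1+(m−1)×0.02]/n) × (critical value + power quantile).

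- Women's diet: n = 1000×0.8 = 800, m = 20, design effect 1.38. 1.57 × sqrt(2×1.38/800) = 0.0922. Times 3.13 (t, 78 df) = 0.289, against 0.29 stated.
- Adult ∑DAPs: n = 150, m = 3.75, design effect 1.055. 111 × sqrt(2×1.055/150) = 13.16. Times 3.083 (normal) = 40.6, against 39.6 stated. With 4 per cluster (160 per arm) it is 39.4. Either way 150 has to mean completers.

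Table 5 is therefore powered on change, which matches equation (1).

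**2. Compare the estimators.** With equal SDs at the two times, variances are proportional to:

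- equation (1): 2(1−r)
- 12-month value only: 1
- baseline-adjusted: 1−r²

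The SE ratio, adjusted to equation (1), is sqrt((1+r)/2): 0.81 at r = 0.3, 0.87 at 0.5, 0.92 at 0.7, 0.95 at 0.8 and 0.97 at 0.9.

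**3. Put r on the cluster scale.** The relevant r is the correlation of cluster means:

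r = [m×ICC×CAC + (1−ICC)×τ] / [1+(m−1)×ICC],

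where τ is the within-person correlation and CAC the cluster autocorrelation. Neither is in the protocol. I assume CAC = 0.8 and τ from 0.3 to 0.5.

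| Outcome | m | τ | r | SE ratio, formula | SE ratio, simulation |
|---|---|---|---|---|---|
| Diet | 20 | 0.3 | (0.32+0.294)/1.38 = 0.445 | 0.85 | 0.86–0.88 |
| Diet | 20 | 0.5 | (0.32+0.490)/1.38 = 0.587 | 0.89 | 0.89 |
| ∑DAPs | 4 | 0.3 | (0.064+0.294)/1.06 = 0.338 | 0.82 | 0.81–0.82 |
| ∑DAPs | 4 | 0.5 | (0.064+0.490)/1.06 = 0.523 | 0.87 | 0.86–0.88 |

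The simulations used 80 clusters, ICC 0.02 and cluster-robust SEs. Both estimators were unbiased for the same effect, and rejection under the null was 0.020–0.028 at nominal 0.025. At τ = 0.85 the SE ratio rose to about 0.96.

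**4. Translate to Table 5.**

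- Women's diet: 0.29×0.86 = 0.249; 0.29×0.89 = 0.258.
- Adult ∑DAPs: 39.6×0.81 = 32.1; 39.6×0.87 = 34.5.

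**5. When is equation (1) worse than ignoring baseline?** Setting r = 0.5 gives τ = (0.69−0.32)/0.98 = 0.38 for diet and (0.53−0.064)/0.98 = 0.48 for ∑DAPs. Below those values it is.

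**6. Does the planned adjustment recover the loss?** In complete baseline and 12-month pairs, β3 is determined by within-person differences. A time-invariant covariate added to equation (1) as a main effect cancels from those differences, so β3 and its SE do not change. Choosing covariates by between-group p-values also targets imbalance, not prognosis.

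**The case against.** The strongest reply is that nothing here is wrong. Equation (1) is unbiased, holds its type I error rate and agrees with the change-scale power in Table 5. The planned detectable differences already lie below the cited prior estimates (0.29 against 0.36 for women's diet, 0.26 against 0.39 for children's). All of that stands.

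The size of the gain also rests on quantities the protocol does not state. If r is 0.8 the SE gain is 5%, and at 0.9 it is 2.5%. Equal SDs are assumed too. With a baseline-to-follow-up SD ratio k, the variance ratio is (k²+1−2rk)/(1−r²). At r = 0.5 this is 1.12 for k = 0.8, 1.33 for k = 1 and 1.65 for k = 1.2, so the gain could be smaller or larger. This matters most for children, whose diets change over the year.

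A reader might infer that about 35% of the sample is wasted. That comes from putting a within-person correlation of 0.3 into 1−(1+r)/2 as if people were independent. Stable village effects raise r for diet, and the corresponding figure is about 1−0.86² = 26%.

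A reader might also infer that the children's effect is confounded with ageing. It is not: ageing is common to both randomised arms, Time absorbs it, and it cancels from β3 in expectation. Age is only a source of noise.

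The planned adjusted models show that precision was considered, but step 6 shows that main-effect adjustment of equation (1) does not supply it.

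**Conclusion.** The point holds as an avoidable loss of precision. The documents do not support reading it as bias, or as a power statement that is too optimistic; the 80% power claimed matches the planned estimator.

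Under the assumptions in step 3 with equal SDs, the SE would fall by roughly 11–14% for dietary diversity and 13–19% for ∑DAPs. In power terms, at Table 5's own detectable differences, 80% becomes Φ(3.083/ratio − 2.241): about 89–91% for diet (ratios 0.89 and 0.86) and 90–94% for ∑DAPs (0.87 and 0.81). At correlations of 0.8 or more the SE gain is about 5% or less. The adjusted analysis was more precise at every correlation simulated.

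One condition applies: baseline must be untouched by allocation. The protocol provides for this, although the allocation list goes to the implementer in confidence before baseline ends.

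**What to change.** Make the primary model the 12-month outcome on group, baseline outcome and district, by GEE clustered on village with robust standard errors. The group coefficient is then the effect.

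Alternatively, keep the longitudinal model and constrain β1 = 0, which also retains people without a baseline value. In that case specify a working correlation that carries the within-person correlation; under working independence the constrained model reduces to the 12-month comparison and gains nothing from baseline.

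Prespecify child age as a covariate, for precision only. Keep equation (1) as a sensitivity analysis, and state the correlation assumed.

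The cost is wording in the analysis plan and no new data. The effect is reported as an adjusted 12-month difference. Plain baseline adjustment drops people with no baseline value, but the planned complete-case analysis of change does the same.
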